## Abstract

**Background:**

While the introduction of neoadjuvant therapy has innovated perioperative treatment strategies for locally advanced gastric cancer (LAGC), preventing postoperative recurrence and metastasis remains a key clinical challenge. Previous research has indicated that Shenqi Fuwei granules (SQFWG), a Traditional Chinese medicine (TCM) prescription, possesses anti-gastric cancer properties. However, evidence from perioperative intervention studies is lacking. Our trial aims to evaluate the efficacy and safety of SQFWG combined with perioperative therapy in reducing postoperative recurrence and metastasis in LAGC, to explore clinical characteristics of the benefiting population, and to provide an evidence base for developing treatment protocols.

**Methods:**

This is a prospective, randomized, double-blind, placebo-controlled, multicenter clinical trial. We plan to recruit 286 perioperative LAGC patients from multiple hospitals in China. Participants will be randomly assigned (1:1) using a central interactive web response system with allocation concealment, stratified by the use of neoadjuvant chemotherapy ± immunotherapy, to either the control group (n=143, placebo containing 5% SQFWG) or the experimental group (n=143, SQFWG). Both groups will concurrently receive perioperative treatment (chemotherapy ± immunotherapy). Follow-up assessments will be conducted every 3 months for 3 years after treatment completion or upon reaching an endpoint event. The primary efficacy endpoint is event-free survival. Secondary outcomes include overall survival, cumulative 1-/2-/3-year recurrence and metastasis rates, surgical conversion rate, quality of life, and safety. At the same time, prespecified subgroup analyses will be performed according to the use of immunotherapy and the type of chemotherapy regimen, and the clinical applicability of SQFWG will be further explored.

**Discussion:**

To our knowledge, this is one of the first multicenter randomized double-blind placebo-controlled trials evaluating the efficacy of SQFWG in perioperative LAGC. This trial is expected to provide high-level evidence for the role of TCM in perioperative comprehensive management of LAGC.

**Clinical trial registration:**

## Introduction

1

Gastric cancer (GC) ranks as the fifth most common malignant tumor globally, estimated 968,400 new cases and 659,900 deaths, making it the second most incidence and the third most mortality in the digestive system (1). The incidence and mortality of GC in China surpass the global average, accounting for 37.04% of new cases and 39.46% of deaths worldwide (2). Due to its non-specific early symptoms, approximately 70% of Chinese patients are diagnosed at an advanced stage. While gastrectomy with D2 lymphadenectomy is the standard surgical treatment for locally advanced gastric cancer (LAGC) (3), about 40-60% of LAGC patients experience postoperative recurrence and metastasis, resulting in a 5-year survival rate below 50% (4). Landmark phase III trials, such as CLASSIC (5), ARTIST (6), RESOLVE (7), RESONANCE (8), PRODIGY (9), and MATTERHORN (10), have established the role of perioperative therapy (neoadjuvant and adjuvant chemotherapy). These regimens improve tumor shrinkage, clinical downstaging, R0 resection rates, and survival outcomes while reducing recurrence, thereby solidifying the perioperative treatment model. Despite these advances, 40.6-48.9% of patients still experience recurrence within three years post-surgery, and 39-47.9% die within five years (4).

The advent of immune checkpoint inhibitors has revolutionized the treatment landscape for advanced GC, spurring investigation into their synergistic potential with chemotherapy in the perioperative setting, as seen in trials like KEYNOTE-585 (11), DRAGON IV (12), and notably MATTERHORN (10). The MATTERHORN study demonstrated the potential of chemoimmunotherapy in resectable LAGC, showing an 8% improvement in 2-year EFS (67% vs. 59%) and a 6.7% improvement in 3-year OS (68.6% vs. 61.9%). Mechanistically, chemotherapy can induce immunogenic cell death and deplete immunosuppressive cell populations in the tumor microenvironment, thereby potentially enhancing the efficacy of concomitant immunotherapy (13, 14). Furthermore, preoperative immunotherapy may prime systemic anti-tumor immunity, while its continuation postoperatively could help eradicate minimal residual disease, collectively reducing recurrence risk. This underpins the “chemo-reduction plus immune-consolidation” strategy evaluated in MATTERHORN, where durvalumab combined with FLOT chemotherapy aimed to shrink tumor burden preoperatively and eliminate residual cells postoperatively (15). Preventing recurrence and metastasis remains a critical bottleneck for improving the prognosis of LAGC, and the introduction of immunotherapy has underscored the urgent need for novel therapeutic strategies.

Accumulating evidence indicates that Traditional Chinese Medicine (TCM) offers unique advantages in cancer prevention, attenuating treatment-related toxicity, enhancing therapeutic efficacy, and reducing recurrence and metastasis (16–19). Only one meta-analysis focusing on postoperative adjuvant chemotherapy combined with TCM for LAGC reported extended DFS by approximately 2.61 months (mean difference [MD]: 2.61 months, 95% CI [1.38, 3.83]), reduced the cumulative 1-, 2-, 3-, and 5-year recurrence/metastasis rates by 39%, 40%, 51%, and 40%, alongside reduced chemotherapy-related toxicities such as myelosuppression and gastrointestinal reactions (20). Furthermore, a recent multicenter prospective cohort study showed that the TCM formula Yiqi Huayu Jiedu Decoction reduced the postoperative recurrence/metastasis rate by 34.7% and improved the 5-year survival rate by 14.24% (85.29% vs. 71.05%) in stage III LAGC (21). This underscores the significant therapeutic potential of TCM as a complementary modality to reduce postoperative recurrence and metastasis in LAGC. However, evidence specifically in the perioperative LAGC setting remains limited, and there is a notable lack of clinical trials evaluating the continuous administration of TCM throughout the entire perioperative period. High-quality evidence is still needed to determine whether integrating TCM into contemporary perioperative therapy for LAGC can effectively reduce recurrence and prolong survival.

The Chinese herbal compound WeiFuFang, developed by [name], a National Master of Chinese Medicine in the Department of Integrated Traditional Chinese and Western Medicine at Hunan Cancer Hospital, was optimized into Shenqi Fuwei Granules (SQFWG) after dosage form improvement. This formulation was registered as a hospital-prepared TCM product with the Hunan Medical Products Administration (Registration No. Xiangyao Preparation Z20240984000). Modern pharmacological studies suggest its active components possess anti-angiogenic, immunomodulatory, and pro-apoptotic properties (22–31). Preliminary clinical studies indicate that this compound could prolong median survival, improve survival rates, enhance quality of life (QoL), and exhibits a favorable safety profile in patients with LAGC (32–35). However, robust evidence from large-scale, multicenter clinical trials is lacking regarding whether SQFWG could improve perioperative outcomes, reduce postoperative recurrence and metastasis, alleviate symptoms, and enhance QoL in LAGC within the contemporary perioperative therapy framework. Therefore, our trial represents the first multicenter effort to evaluate the integration of TCM compound with perioperative therapy, aims to determine the clinical efficacy and safety of SQFWG combined with neoadjuvant/adjuvant chemotherapy ± immunotherapy in reducing postoperative recurrence and metastasis in LAGC.

## Methods

2

### Study design

2.1

This study is a multicenter, randomized, double-blind, placebo-controlled clinical trial conducted in China. It will be implemented across at least seven tertiary hospitals, including Hunan Cancer Hospital, Xiangya Hospital of Central South University, Guangdong Provincial Hospital of Traditional Chinese Medicine, Jiangsu Provincial Hospital of Traditional Chinese Medicine, the First Affiliated Hospital of Hunan University of Traditional Chinese Medicine, and Guangxi International Zhuang Medical Hospital. Central randomization with allocation concealment will be employed, stratified by the use of neoadjuvant chemotherapy ± immunotherapy. All participants will receive perioperative chemotherapy (SOX or XELOX) ± immunotherapy. In addition, patients in the experimental group will receive SQFWG, while those in the control group will receive a matched placebo containing 5% SQFWG. The study medication will be administered concurrently with chemotherapy and continued until disease progression, unacceptable toxicity, or completion of the perioperative treatment phase. All patients will be followed for 3 years. After completing the final treatment or upon reaching a study endpoint, patients will enter a follow-up phase with assessments scheduled every 3 months. The primary efficacy endpoint is event-free survival (EFS). **Figure 1** presents the flowchart for participant enrollment, intervention, and assessment. **Figure 2** illustrates the schedule of interventions and follow-up. The study phases are outlined in **Table 1**.

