### Sample size calculation

2.5

This is a randomized, placebo-controlled superiority trial with a 1:1 allocation ratio. The primary endpoint is EFS. Based on the KEYNOTE-585 trial results (11), the assumed 3-year EFS rate for the control group (receiving perioperative chemotherapy ± immunotherapy) is 44%. We hypothesize that the addition of SQFWG will increase the 3-year EFS rate by 20% (absolute improvement), resulting in a rate of 64% for the experimental group. Using a two-sided significance level (α) of 0.05 and a power (1-β) of 80%, and assuming a constant accrual rate over an enrollment period of 36 months, the sample size was calculated using PASS software (version 15). This calculation yielded 114 participants per group. To account for an estimated 20% dropout rate, the final target enrollment is set at 143 participants per group. The design is event-driven, requiring a sample size of 286 cases. The duration of enrollment is 3 years, and the total study duration is 5 years, taking into account a 20% dropout rate.

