### Data collection and management

2.8

Source data will be collected using electronic case report forms within a secure, web-based Electronic Data Capture (EDC) system. Site investigators will be responsible for data entry. All study personnel will receive standardized training on the study protocol and data entry procedures.

Data management will be facilitated by a multi-center research collaboration platform - a validated EDC system hosted by Beijing Bioknow Information Technology Co., Ltd. This platform provides secure data collection, tracking, validation, and export functionalities.

Two independent clinical research coordinators will perform double data entry. The EDC system will then compare entries for verification. Following this, investigators will review and confirm the data. All data changes will be logged in the system’s audit trail. Participants will be identified by unique codes to ensure confidentiality. The principal investigator will bear overall responsibility for data integrity.

An independent Data Monitoring Committee (DMC) will periodically review data quality and safety, which empowered to recommend modifications to the trial (dose adjustment, sample size re-estimation) based on interim analyses of accrued data. The study database will be locked after resolving all data queries and completing final participant follow-up.

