## Trial status and progress

3

Funding sources: the Noncommunicable Chronic Diseases–National Science and Technology Major Project (Grant Nos. 2024ZD0521301 and 2024ZD0521300), 2024.12-2028.11.

Recruitment start date: November 1, 2025; expected completion: August 30, 2028.

Expected primary analysis completion: December 2030.

Expected primary results publication: anticipated in 2031 after completion of follow-up.

Number of recruited participants at submission: 61 (as of 2026.7.9).

Data collection is ongoing at the time of protocol submission; no data analysis has been performed.

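### Three years of follow-up for every patient does not fit the stated 5-year study or the December 2030 analysis, and the 3-year rates defined as simple proportions suffer for it

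*Protocol article*

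**What the plan says.** The protocol article describes follow-up and the end of the trial in five places:

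- Section 2.1: "All patients will be followed for 3 years". No time origin is given.
- Abstract, Methods: "Follow-up assessments will be conducted every 3 months for 3 years after treatment completion or upon reaching an endpoint event".
- Section 2.5: "The duration of enrollment is 3 years, and the total study duration is 5 years, taking into account a 20% dropout rate". The sample size was derived "assuming a constant accrual rate over an enrollment period of 36 months". The same section calls the design event-driven but gives no number of events.
- Section 3: "Recruitment start date: November 1, 2025; expected completion: August 30, 2028", then "Expected primary analysis completion: December 2030". Publication is anticipated in 2031, once follow-up is complete.
- Section 2.8: "The study database will be locked after resolving all data queries and completing final participant follow-up".

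Three other places bear on the consequences. Section 2.3 keeps the randomization schedule sealed until database lock, except for emergency unblinding. Section 2.7.2 defines the 1-, 2- and 3-year recurrence/metastasis rates as proportions of patients from randomization, and the survival rates as proportions from surgery. Section 2.9 places the recurrence/metastasis rates in the fixed-sequence testing that follows EFS.

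**The concern.** If enrolment takes 3 years and every patient is followed for 3 years, the study lasts 6 years. It lasts longer if the 3 years begin after treatment. A 5-year study leaves 2 years for the last entrant. Nothing in the article says that late entrants are followed for less time than the others.

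Two things are at stake. The first is operational: sites cannot tell when a patient's visits end, and data management cannot tell when to lock. The second is statistical: a 3-year rate written as a plain proportion needs 36 months of observation on every patient in its denominator. If some patients cannot have that, counting them as recurrence-free understates the rate. Dropping those without 36 months while keeping early recurrences overstates it. One such rate is formally tested.

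**Working it through.** **Inputs.** Enrolment 36 months and total duration 60 months (section 2.5). Recruitment 1 November 2025 to 30 August 2028, primary analysis December 2030 (section 3). Total 286 patients, uniform accrual, 3-year EFS 44% and 64% (section 2.5). Assumptions made here: a cut-off of 31 December 2030, exponential EFS and no dropout.

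**The plan's own total.** 60 − 36 = 24 months for the last patient. Five years from 1 November 2025 is 1 November 2030, close to the December 2030 analysis. Sections 2.5 and 3 therefore roughly agree with each other. The abstract and section 2.1 do not agree with them.

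**Last patient on the calendar dates.** From 30 August 2028 to 31 December 2030 is 28.0 months (27.0 months if the cut-off is 1 December). Thirty-six months from randomization ends on 30 August 2031, which is 69.9 months after the start. Under the abstract's rule the end falls later still. The stated 6 to 10 three-week cycles (section 2.6) add 18 to 30 weeks, which gives about January to March 2032 before any time for surgery.

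**Share unable to reach 36 months from randomization.**

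- Calendar dates: recruitment lasts 1033 days. Patients entering after 31 December 2027 fall short, and that window is 243 days. 243/1033 = 23.5%, and 0.235 × 286 ≈ 67. With a cut-off of 1 December 2030 it is 273/1033 = 26.4%, about 76.
- 36+24-month plan: 12/36 = 33%, about 95.

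**Share censored event-free before 36 months.** Monthly hazards are −ln(0.44)/36 = 0.02281 and −ln(0.64)/36 = 0.01240. For potential follow-up spread uniformly from a to 36 months, the mean event-free probability in an arm is [exp(−λa) − exp(−36λ)] / [λ(36 − a)].

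| Timeline | a (months) | Control | Experimental | Mean | Patients | Share of 286 |
|---|---|---|---|---|---|---|
| Calendar dates | 28.0 | 0.483 | 0.673 | 0.578 | 67 × 0.578 ≈ 39 | 14% |
| 36+24 plan | 24 | 0.506 | 0.690 | 0.598 | 95 × 0.598 ≈ 57 | 20% |

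**Does this threaten the primary test?** HR = ln(0.64)/ln(0.44) = 0.544. Schoenfeld's formula needs 4(1.960 + 0.842)²/(ln 0.544)² ≈ 85 events; Freedman's needs 90. With 3 years of accrual and 5 years in total, the event probability per arm is 1 − [exp(−2λ) − exp(−5λ)]/(3λ), with λ per year. This gives 0.605 and 0.401, mean 0.503, so 286 × 0.503 ≈ 144 events. Allowing for 20% lost by 3 years gives about 128. Both exceed the requirement.

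**The case against.** The strongest defence is that December 2030 is a primary analysis that precedes the end of follow-up. The last patient would then complete 3 years from randomization on 30 August 2031, which fits publication in 2031 after follow-up is complete. As to dates, this works if the 3 years run from randomization, and the dates in section 3 are labelled as expected. It fails on the article's own procedures: lock waits for the final participant's follow-up (section 2.8) and the allocation schedule stays sealed until lock (section 2.3). A between-group analysis in 2030 would break one of these. Under the abstract's time origin, publication in 2031 fails as well.

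It is also fair to say that shorter follow-up for late entrants is ordinary, and that Kaplan-Meier, log-rank and Cox methods (section 2.9) accommodate it. That stands.

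Three stronger readings should be resisted:

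- A reader might infer that up to half of the patients lack the needed follow-up. Counting 3 years from the end of treatment does give 36% to 52%, depending on treatment length and the December date, but the upper end needs an assumed 8 weeks around surgery. That share also does not bear on EFS, OS or the recurrence rates, which run from randomization.
- A reader might infer that the EFS comparison is invalid or underpowered. The event counts do not support this.
- A reader might count four incompatible end-of-trial rules. The lock sentence only inherits whichever follow-up length applies, and the event-driven label has no number that could conflict with a date. The real conflict is between follow-up length, with its origin, and study duration.

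**Conclusion.** The contradiction is real and rests on the article's own durations and dates, so a separate analysis plan cannot remove it: 36 months do not fit into 24 to 28. Between 23.5% and 33% of patients cannot reach 36 months from randomization, assuming uniform accrual. About 14% to 20% of all patients would be censored event-free before that point, assuming exponential EFS at the planned rates and no dropout.

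The damage is limited but concrete. The study duration and lock date cannot be followed as written. The 3-year recurrence/metastasis rate, which is part of the formal testing sequence, and the 3-year survival rate are biased or undefined as simple proportions. The survival rate is the more exposed of the two, because its clock starts at surgery, after 2 to 4 preoperative cycles.

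**What to change.** State one follow-up rule and one time origin for it in the abstract and in sections 2.1, 2.5, 2.8 and 3. There are two workable options.

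**(a) Common cut-off.** Follow all patients to a single data cut-off at least 24 months after the last randomization, and tie lock for the primary analysis to that cut-off. Either remove the event-driven label or give the number of events. Estimate 3-year EFS and survival by Kaplan-Meier, and 3-year recurrence/metastasis by cumulative incidence with death as a competing event. This keeps the December 2030 date. It costs an amendment to the wording and to the definitions in section 2.7.2, and late entrants will have less than 3 years of follow-up at the primary analysis. It also changes the follow-up stated when the 61 patients already recruited were enrolled, so it should say whether their visits continue after the cut-off.

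**(b) Three years for all.** Keep 3 years from randomization for every patient and restate the primary analysis as no earlier than 30 August 2031. That is about 70 months from the start on the calendar dates, or 6 years with a full 36-month accrual. If the 3 years are to run from treatment completion, the date moves further, into 2032. The cost is a delay of 8 months or more. Loss to follow-up would still call for the censoring-aware estimates in (a).

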**Figure 1 f1:**
[figure not shown]
Flowchart of treatment phases.

**Figure 2 f2:**

Intervention and follow-up flow chart.

**Table 1 T1:** The schedule of participants.

Project			Lead-in period	Intervention period						Follow-up period ^[2]^
				Preoperative visit (2 ~ 4 cycles)		Operation	Postoperative visit (4 ~ 6 cycles)			
Timepoint			V0	V1	VN		Postoperative V1	Postoperative V2	Postoperative VN	N+V
Visit date			-W1-0W	W3 ± 1W	WN*3 ± 1W	Date of operation	Postoperative ± 4W	WN*3 ± 1W	WN*3 ± 1W	Every 3 months ± 1M
Inclusion/exclusion criteria			✓							
Signed informed consent			✓							
Collected medical history										
demographic data			✓							
diagnosis			✓							
Past history and concomitant diseases			✓							
Therapeutic observation										
Vital signs			✓	✓	✓		✓	✓	✓	*
Physical examination			✓	✓	✓		✓	✓	✓	*
Physical condition score			✓	✓	✓		✓	✓	✓	✓
MDASI-TCM			✓	✓	✓		✓	✓	✓	
Description of tongue and pulse			✓	✓	✓		✓	✓	✓	
TCM syndrome			✓	✓	✓		✓	✓	✓	
Imaging Examination^[1]^	CT		✓	Repeated every 2–3 courses during treatment						*
	MRI, B-ultrasound		*							*
	Bone scanning		*							*
	Gastroscope		*							*
Tumor marker			✓	✓	✓		✓	✓	✓	*
FACT-Ga			✓	✓	✓		✓	✓	✓	
ESAS			✓	✓	✓		✓	✓	✓	
Infections and Complications Assessment ^[3]^							✓			✓
Safety observation										
Routine blood/ urine/stool			✓	✓	✓		✓	✓	✓	*
Liver/kidney function			✓	✓	✓		✓	✓	✓	*
ECG			✓	✓	✓		✓	✓	✓	*
NCI-CTCAE				✓	✓	✓	✓	✓	✓	✓
AEs				✓	✓	✓	✓	✓	✓	✓
Biological Sample Collection										
Biological Sample Collection		blood	✓			√ Preoperative Collection			√ (End of treatment/Progression)	
		urine								
		stool								
		Tongue coating								
		Pathological tissue				✓				
Other work										
Drug combination				✓	✓		✓	✓	✓	✓
Efficacy evaluation				✓	✓		✓	✓	✓	✓
Medication compliance			✓	✓	✓		✓	✓	✓	✓

* in the table indicates that this check is optional. ^[1]^For imaging examinations, the same examination method should be used for screening of the same site and for each review after enrollment, and the examination should be reviewed every 2–4 sessions during the treatment phase and every 3 months during the follow-up phase. Head, chest, and abdominal examinations should be selected as appropriate. If CT/MRI examination has been done for the same site, abdominal X-ray examination and ultrasound examination are not necessary. Bone scanning examination is selected according to the patient's condition. ^[2]^Follow-up period: The entry nodes were ① completion of established perioperative treatment (chemotherapy ± immunotherapy), ② disease progression, and ③ intolerable toxicity, and the above conditions were selected. The follow-up period was based on the subject 's hospital selection for in-hospital visits/telephone visits. Vital signs, physical examinations, and other ancillary tests are optional and may not be done at telephone visits. If the subject completes relevant auxiliary examinations in another hospital, the examination results should be collected. [3] Assessment of infection and complications: Complications were assessed only in the early (30 days) and late (12 months) postoperative period.

MDASI-TCM, M.D. Anderson Symptom Traditional Chinese Medicine. TCM, Traditional Chinese Medicine. CT, Computed Tomography. MRI, Magnetic Resonance Imaging. FACT-Ga, Functional Assessment of Cancer Therapy - Gastric. ESAS, Edmonton Symptom Assessment System. ECG, Electrocardiogram. NCI-CTCAE, National Cancer Institute-Common Terminology Criteria for Adverse Events. AEs, Adverse Events.

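### Table 1 makes follow-up tumour imaging optional while its own footnote asks for it every 3 months, and the on-treatment intervals also differ, so EFS events can be dated inconsistently, late or missed

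*Protocol article*

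**What the plan says.** Four places in the protocol article bear on when tumours are imaged.

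- **Table 1, imaging rows.** During treatment, CT is "Repeated every 2–3 courses during treatment". In the follow-up column, CT, MRI/ultrasound, bone scan and gastroscopy all carry an asterisk. The legend says that the asterisk "in the table indicates that this check is optional".
- **Footnote 1**, attached to the imaging rows: "the examination should be reviewed every 2–4 sessions during the treatment phase and every 3 months during the follow-up phase".
- **Footnote 2**, on the follow-up period: contact follows the "hospital selection for in-hospital visits/telephone visits", and "Vital signs, physical examinations, and other ancillary tests are optional and may not be done at telephone visits". It adds one safeguard: "If the subject completes relevant auxiliary examinations in another hospital, the examination results should be collected".
- **Section 2.1** schedules follow-up assessments every 3 months but does not say whether imaging is among them. Table 1 gives the follow-up visits as "Every 3 months ± 1M".

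Section 2.7.1 counts three kinds of EFS event, timed from randomization: progression that rules out curative surgery, recurrence, and death. Table 1 ticks efficacy evaluation as required at every follow-up visit.

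**The concern.** Two of the three EFS components are disease findings whose recorded date depends on when someone looks. One site can follow Table 1 and footnote 2 and never scan a patient in follow-up. Another can follow footnote 1 and scan every 3 months. Both would be within the protocol, yet their EFS dates would not be comparable. Efficacy evaluation is compulsory at each follow-up visit, but no imaging is compulsory to support it.

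The same dates feed DFS and the 1-, 2- and 3-year recurrence/metastasis rates (section 2.7.2). Section 2.9 places both in the fixed testing sequence that opens if EFS is significant. A recurrence that is never imaged either drops out of the analysis or reappears later, as a symptomatic relapse or a death.

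**Working it through.** The plan gives no figure for this point. The main check sets the passages side by side; a power calculation then shows the scale.

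**1. Follow-up.**

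| Source | Imaging in follow-up |
|---|---|
| Table 1, asterisk | optional for every method |
| Footnote 2 | ancillary tests optional; may be omitted at telephone visits |
| Footnote 1 | every 3 months |
| Section 2.1 | assessments every 3 months, imaging not named |

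If footnote 1 governs, the ± 1 month window allows gaps between consecutive visits of 3 − 2 = 1 month to 3 + 2 = 5 months. If the table governs, there is no maximum gap. The asterisk is not a table-reading artefact, because footnote 2 says the same thing in words.

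**2. On treatment.** Section 2.6 gives 3-week cycles. Taking a session as one cycle:
- Table 1: 2 × 3 to 3 × 3 = 6 to 9 weeks.
- Footnote 1: 2 × 3 to 4 × 3 = 6 to 12 weeks.

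Section 2.6 allows 2–4 preoperative cycles. At the table's upper limit, only a patient with 2 cycles could reach surgery before a scan falls due. At the footnote's upper limit, a patient with 2 or 3 cycles could. This bears on the progression component.

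**3. Scale of the harm.** Inputs from section 2.5: 3-year EFS 44% and 64%, two-sided α 0.05, 114 per arm before the dropout allowance, 36 months' enrolment, 60 months in total. Assumptions of this check: exponential EFS, uniform accrual (so follow-up of 24 to 60 months), no dropout, and events lost equally in both arms with the hazard ratio unchanged.

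- Monthly hazards: −ln(0.44)/36 = 0.0228 and −ln(0.64)/36 = 0.0124. Hazard ratio = ln(0.64)/ln(0.44) = 0.544, so |ln HR| = 0.6095.
- Probability of an event, averaged over the two arms: 0.503. Expected events: 228 × 0.503 ≈ 115.
- Power (Schoenfeld) = Φ(√d/2 × |ln HR| − 1.96). For d = 114.7: √114.7/2 × 0.6095 − 1.96 = 1.30, giving 0.90.
- Events needed for 80% power: 4 × (1.96 + 0.8416)²/0.6095² = 84.5, so 85.

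| Share of events never captured | Events, from 115 | Power | Power, starting from 85 events |
|---|---|---|---|
| 0% | 115 | 0.90 | 0.80 |
| 10% | 103 | 0.87 | 0.76 |
| 20% | 92 | 0.83 | 0.71 |
| 30% | 80 | 0.78 | 0.65 |

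The last column covers a trial that yields only just enough events.

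**4. Late but not lost.** A log-rank simulation on the same assumptions (600 runs per scenario) dated each event to the next assessment. Power was about 0.91 with 3-monthly detection in both arms and 0.88 with 6-monthly detection in both. The simulation error is about 0.012 on each figure, so the two are barely distinguishable. Type I error was about 0.04 in both cases, within error of 0.05. Equal delay in both arms therefore costs little; losing events costs more.

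**The case against.** The strongest reply is that footnote 1 is attached to the imaging rows and gives a plain 3-monthly instruction. On that reading the asterisks mean only a choice of method, with some imaging still due. Required efficacy evaluation at every follow-up visit and the 3-monthly assessments in section 2.1 point the same way. This reading is possible, but the text never states it, and footnote 2 goes against it by making ancillary tests optional without excepting imaging.

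Several limits on the harm do stand. Deaths are captured whatever the imaging. Results from other hospitals are to be collected. The 2–3 against 2–4 mismatch is minor beside the follow-up conflict. Counting scans in courses is a design choice and contradicts nothing.

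A reader might go further and infer that the loose schedule biases EFS towards one arm, for example because the granules could change chemotherapy delivery and so the timing of course-based scans. The documents do not support that. Section 2.4 blinds participants, investigators and outcome assessors, including imaging evaluators, so visit mode and scan timing are chosen without knowledge of the arm. Nothing in the documents suggests different scan intervals or telephone rates by arm. Cycle delay would touch only the on-treatment scans.

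**Conclusion.** The point holds as an internal contradiction affecting the primary endpoint. Follow-up imaging is optional in Table 1 and footnote 2 but 3-monthly in footnote 1, and the on-treatment intervals disagree. No single enforceable schedule exists for detecting recurrence or progression. The follow-up conflict must be fixed; the on-treatment mismatch can be settled in the same correction.

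The consequence is a possibility, not a certainty: events can be dated inconsistently, late or missed. It would be too strong to say that they will be, because many sites may follow footnote 1. The expected cost is lost events and lower precision. Power falls from about 0.90 to 0.87, 0.83 or 0.78 at 10%, 20% or 30% of events lost. These figures rest on the exponential model, no dropout, an unchanged hazard ratio and an assumed share of missed events.

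**What to change.** Reconcile Table 1, footnotes 1 and 2 and section 2.1 into one imaging schedule, on treatment and in follow-up, with the interval confirmed by the clinical team. Within it:

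- remove the optional mark from tumour imaging for patients still without an EFS event;
- apply the schedule identically in both arms;
- state that a telephone contact does not replace a due scan, while a result from another hospital may count.

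As an option, add an EFS sensitivity analysis that back-dates events found after a missed scan to the first missed due date.

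The cost is a corrected table and footnotes and a memo to sites. If the clinical team keeps the 3-month interval, no patient has more follow-up imaging than footnote 1 already asks for, although a site that has worked from the asterisks would need to do more than it does now. Section 3 reports 61 participants already recruited, so the correction should reach sites soon.
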